## Clinical trial objectives

### Hypothesis I

Administration of oral NAC at a dose of 900 mg daily in combination with second-line during treatment of multidrug-resistant tuberculosis (MDR-TB) will protect against occurrence of serious advent events without interfering with the effect of second line anti-TB regimen.

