## Trial design

NAC trial is a phase 2b randomized open labelled superiority trial with three parallel groups and a primary endpoint of occurrence of ADRs at any time during treatment for MDR-TB.

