### Additional consent provisions for collection and use of participant data and biological specimens

Additional consent will be administered for phlebotomy for full pharmacokinetic sampling, which will be performed at 2 weeks after initiation of treatment. The consent will cover week 2 venous blood collection that will be drawn at 1, 2, 6, and 10–12 (late sample per site feasibility) hours and week 8 drawn at 2 and 6 h after medication administration with attempt by single venipuncture for peripheral IV insertion. Such sampling allows for adequate calculation of serum peak (*C*_max_) and estimate total exposure (AUC) of the MDR-TB drugs in the regimen to determine if NAC co-administration unexpectedly impacts these parameters. A maximum of 7 ml will be obtained in heparinized tubes at each draw as up to 4 drugs will be required to be assayed. Additional consent will be obtained for other baseline specimens like stool, urine and saliva for pre-planned future studies.

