### Sample size

This is a pilot trial to collect information about the effect of NAC that will potentially guide a future larger trial, thus there was no formal power calculation. Therefore, the sample size for the proposed trial will be 20-per arm and thus 60 participants will be enrolled for three arms. However, previously we have found a withdrawal/non-evaluable subject rate from our previous TB clinical trials estimated at 10% [33]. Therefore, a total of 66 MDR-TB patients will be recruited for this clinical trial [34].

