## Statistical methods

### Statistical methods for primary and secondary outcomes

The primary efficacy analysis will be conducted using laboratory measurement. Analysis that will be performed includes both Modified Intent to Treat (MITT) defined as analysis of all randomised participants and a Per Protocol (PP) defined as comparison of three arms; control with either 900 mg OD or 900BD or both intervention arms in participants who completed the treatment originally allocated.

The difference in the proportion of patients with ADRs (as defined by the primary efficacy endpoint) between each treatment arm and control arm will be calculated with 95% confidence interval using standard methods**.** In addition, hearing threshold level will be analysed over time using mixed effect models to account for the longitudinal nature of the data. Mean differences between arms in change from baseline (with 95% confidence intervals) will be derived from the fitted model.

The incidence of severe adverse drug reactions as defined by Common Terminology Criteria for Adverse Event (CTCAE) will be calculated in percentage of affected individuals in each arm during the exposure time period of 6 months and the relative risks will be estimated. Time to stable conversion in both phenotypic and molecular (TB molecular bacterial load assay) MTB monitoring methods will be calculated and compared in each arm using adjusted and unadjusted hazard ratio with log-rank test. Furthermore, the rate of patients in each arm converting to negative sputum culture at 4 or 6 or 8 months after treatment initiation will be estimated. Kaplan-Meir estimator will be used to estimate the proportion of patients converting to negative culture and MBLA by specific time.

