### Pharmacokinetics analysis

Plasma concentrations will be used to build a population PK models to evaluate the effects of NAC on the distribution, metabolism, and excretion of MDR-TB drugs.

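### A log-rank test of no difference cannot support the non-interference half of Hypotheses I and II, and no accompanying analysis sets a bound

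*Protocol article*

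**What the plan says.** Hypothesis I (900 mg daily) and Hypothesis II (900 mg twice daily) of the protocol article each join a protective claim to a second one, that NAC acts "without interfering with the effect of second line anti-TB regimen". Neither gives a numerical limit. The Trial design section describes a "randomized open labelled superiority trial with three parallel groups" and names no non-inferiority or equivalence component.

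Four parts of the plan bear on the second claim:

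- Time to stable conversion, by culture and by the molecular bacterial load assay, "will be calculated and compared in each arm using adjusted and unadjusted hazard ratio with log-rank test" (Statistical methods for primary and secondary outcomes).
- In the same section, the rate of patients "converting to negative sputum culture at 4 or 6 or 8 months after treatment initiation will be estimated", with Kaplan-Meier estimates of the proportion converted.
- Sampling for peak concentration and exposure of the MDR-TB drugs, "to determine if NAC co-administration unexpectedly impacts these parameters" (Additional consent provisions for collection and use of participant data and biological specimens).
- A population model "to evaluate the effects of NAC on the distribution, metabolism, and excretion of MDR-TB drugs" (Pharmacokinetics analysis).

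None of these sets a largest acceptable slowing, a bound on exposure, or a rule for concluding that NAC does not interfere. On size, the Sample size section plans 20 per arm, raised to 66 in total, and describes a pilot, "thus there was no formal power calculation".

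**The concern.** A claim that an added drug does no harm to the background regimen needs evidence that excludes harm beyond some limit. The log-rank test asks whether the data contradict equal conversion. Failing to reject equality is a different result from excluding a slowing, and this is true at any sample size. A very large trial could reject equality because of a trivial delay. A small one will usually fail to reject it even when the delay is large, so the less information there is, the more reassuring the p-value tends to look.

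What is at stake is what the trial may say about interference. The article states that its evidence will guide a later pragmatic trial. If a non-significant p-value were carried forward as a finding of no interference, a real slowing of bacterial clearance could go with it.

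**Working it through.** **The plan's own figure.** The only figure to reproduce is the total sample size: 60 × 1.10 = 66. (Dividing instead, 60 / 0.90 = 66.7, gives 67; the difference does not matter here.) The article gives no power, margin or event count for conversion.

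**Inputs.** From the article: 20 evaluable or 22 recruited per arm, 1:1:1 allocation, monthly sputum. Assumed, because not stated:

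- Conversions per pairwise comparison, *d*: from 0.80 × 40 = 32 to all 44 recruited.
- A two-sided 5% level, in line with the ADR difference, which "will be calculated with 95% confidence interval using standard methods".
- Hazard ratio (HR) written as NAC over control, so that values below 1 mean slower conversion.

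**Precision and power.** With equal arms, SE(log HR) = √(4/*d*). The 95% interval is HR divided and multiplied by exp(1.96 × SE). The chance of a non-significant result at a true HR is approximately 1 − Φ(|ln HR|/SE − 1.96).

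| *d* | SE | Interval factor | Significant only if observed HR is below | Non-significant at true HR 0.50 | at 0.67 | at 0.80 |
|---|---|---|---|---|---|---|
| 32 | 0.354 | 2.00 | 0.50 | 50.0% | 79.6% | 90.8% |
| 40 | 0.316 | 1.86 | 0.54 | 40.8% | 75.6% | 89.5% |
| 44 | 0.302 | 1.81 | 0.55 | 36.7% | 73.6% | 88.9% |

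An observed HR of exactly 1.0 would thus have an interval of 0.50 to 2.00 with 32 events, or 0.55 to 1.81 with 44.

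**Check by simulation.** Log-rank tests were simulated with 20 and 22 per arm, exponential conversion, monthly visits, follow-up to month 6 and an assumed control median of 1 to 3 months (3,000 replicates per setting). The test was non-significant in 42% to 59% of trials at a true HR of 0.50 and in 77% to 82% at 0.67. With the slowest control median and 20 per arm, the mean event count under no effect was about 30, just below the assumed range. Follow-up to month 8, when conversion is also assessed, would add some events.

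**How little a non-significant result tells.** It occurs in 95% of trials when there is no effect. Compared with a true HR of 0.67, it is 95/79.6 = 1.2 to 95/73.6 = 1.3 times as likely under no effect. Compared with 0.50, it is 95/50.0 = 1.9 to 95/36.7 = 2.6 times as likely.

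**What such slowing means.** Take a control median of 2 months (assumed) and exponential conversion. The proportion converted by month 6 is 1 − 0.5^(3 × HR): 87.5% at HR 1, 75.2% at 0.67 and 64.6% at 0.50.

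**Pooling does not rescue it.** With both NAC arms against control (48 to 66 events, allocation 2:1), the test is still non-significant in 24% to 38% of trials at HR 0.50 and in 67% to 74% at 0.67.

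**Could a margin be tested with power?** Events needed for 80% power, one-sided 2.5%, true HR 1: 4 × (1.960 + 0.842)² / (ln margin)². For a margin of 0.50 this is 31.4 / 0.480 = 65.3, so 66; for 0.67 it is 196. At most 44 patients are available per comparison. These margins are illustrations only.

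**The case against.** The strongest reply is that the error is not written down. A reader might infer that the protocol will declare non-interference when the log-rank test is non-significant. No sentence says so; the article says only that conversion times are compared. That objection stands, and the point is therefore about what the named test cannot support, not about a decision rule that the plan contains.

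A reader might also infer that interference is examined by the log-rank test alone. That is not so either. The same sentence provides adjusted and unadjusted hazard ratios, conversion proportions and Kaplan-Meier estimates follow, and the pharmacokinetic work addresses interference at the level of drug exposure. These reduce the gap but do not close it. None carries a bound, and exposure is not bacterial response.

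Third, this is a pilot without formal power, its primary objective is exploratory, and conversion is a secondary endpoint, so a powered non-inferiority test would be out of proportion. That is right, and none is asked for. But a pilot disclaimer does not change what a null test can show, and the two hypotheses are worded as firm claims.

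Finally, details such as the model for the listed rate of change of sputum MTB RNA may sit in an analysis plan that is not shown. Its absence from the article is no fault, and choosing that slope as the lead measure would be a preference.

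**Conclusion.** The point holds as a mismatch between two stated hypotheses and the one between-arm test named for anti-TB response. The mismatch is one of logic and does not depend on sample size. The sample size determines how misleading a non-significant p-value could be. Under the assumed 32 to 44 conversions per comparison and a two-sided 5% level, such a result is compatible with conversion at about half the control rate. It would occur in roughly three-quarters to four-fifths of trials in which NAC truly cut the conversion rate by a third.

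Event counts, control medians, significance level and margins are assumptions, but the conclusion is the same across the ranges tried. This is a cheap improvement to what the trial may conclude. It is not evidence that NAC interferes, nor that the trial team intends to claim that it does not.

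**What to change.** In Statistical methods for primary and secondary outcomes:

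1. Base any statement on non-interference on the planned conversion hazard ratio for each NAC arm versus control with its 95% confidence interval, not on the log-rank p-value.
2. Report the largest slowing still compatible with the data (the lower limit of that interval) and set it against a slowing of concern. The trial team should fix that figure without sight of outcome data by arm. This matters because the trial is open label and already recruiting, so fixing it merely before database lock would not be enough.
3. State that a non-significant log-rank result is not evidence of non-interference.

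Alternatively, reword the non-interference part of Hypotheses I and II as exploratory estimation.

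The cost is wording only, since the monthly sputum data are already planned. The downside is that the trial will probably have to report that interference was not excluded.

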### Methods in analysis to handle protocol non-adherence and any statistical methods to handle missing data

We will report clearly any missing data and deploy multiple imputations under the missing at random assumptions for the missing outcomes or covariates, which we anticipate to minimal and not systematic.

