### Adverse event reporting and harms

Adverse events will be collected by the investigator from the time a subject sign the Informed Consent Form through to their end of follow-up visit. Participants that will be early withdrawn, will only have SAEs collected at the time of withdrawal. Any AE (serious or non-serious) observed by the investigator or reported by the subject will be recorded on the Adverse Event Case Report Form. The investigator will review each AE and assess its severity and relationship to drug treatment based on all available information at the time of the completion of the case report form. AE with relationship with drug treatment will be termed as ADRs and severity grading will be according to the CTCAE.

In the case where an overall diagnosis cannot be made, each specific sign and/or symptom will be recorded as individual AEs. Documentation of the date of onset, and stop date (duration) if applicable will be done. The AEs will also be described in severity, and action taken with IMP while concurrently describing the action taken to the participant. The outcome and relationship to IMP will be recited. Also, the occurrence and seriousness of the AEs will be documented.

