## Discussion

This trial is part of the clinical trial capacity development in Tanzania. To our knowledge, this is the first registered trial to examine the protective effect of NAC on occurrence of ADRs in MDR-TB patients treated with current WHO recommended regimens that prioritize bedaquiline, fluoroquinolones, linezolid, and clofazimine. While this new prioritization removes some renal and hearing loss potential if the injectable aminoglycoside is withheld, there remains considerable risk for hepatoxicity from the combination of bedaquiline, clofazimine and a fluoroquinolone, as well as linezolid related cytopenias and neuropathy. Severe ADRs are independently morbid, but resulting treatment interruptions can also amplify *M. tuberculosis* drug-resistance which is particular concern for loss of efficacy of the novel drugs such as bedaquiline [35]. NAC has been recommended as an adjuvant therapy in certain TB and non-TB settings but currently few programmes have adopted this approach in part due to lack of evidence. NAC trials conducted in DS-TB showed not only a protective effect in DILI but also a delayed onset and hastened resolution of DILI if it did occur [36]. Furthermore, a large cohort study revealed that patients that received pulmonary TB treatment and NAC had a substantial reduction in 90-day all-cause mortality compared to those that did not receive NAC [37].

While NAC may provide an opportunity of reducing severe ADRs, it will be important to determine if NAC causes any adverse events independent of the MDR-TB regimen. A pooled analysis of 83 studies (*N* = 9988) that did not include people treated for MDR-TB described the safety of administration of NAC for > 6 weeks. Important adverse events included the gastrointestinal intolerance such as nausea, vomiting, abdominal pain which increased 1.4–2.2 times compared to those that did not get NAC [22]. Given this potential, and the fact that NAC has not been trialed in within a patient population on current WHO recommended medication regimens for MDR-TB, there is clinical equipoise for our proposed trial design.

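### The Kaplan-Meier estimate of the proportion converting has no stated rule for death before conversion; if deaths are censored, it modestly overstates that proportion

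*Protocol article*

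**What the plan says.** Under *Statistical methods for primary and secondary outcomes*, the protocol article plans three analyses of conversion:

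- Time to stable conversion, by culture and by the molecular bacterial load assay, is to be "compared in each arm using adjusted and unadjusted hazard ratio with log-rank test".
- The plan will also estimate "the rate of patients in each arm converting to negative sputum culture at 4 or 6 or 8 months after treatment initiation". No denominator is attached to this rate, although the same section defines its modified intention-to-treat set as everyone randomised.
- Finally, the "Kaplan-Meir estimator will be used to estimate the proportion of patients converting to negative culture and MBLA by specific time".

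None of the three carries a rule for a participant who dies before converting. The section on missing data says the trial will "deploy multiple imputations under the missing at random assumptions for the missing outcomes or covariates" and does not mention deaths. Conversion is listed among the secondary efficacy endpoints. Mortality is not a listed endpoint.

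**The concern.** The plan ties a named estimator to a named quantity, and under the estimator's usual convention the two do not match. A participant who dies unconverted can never convert. Censoring that participant treats them as if they would have gone on to convert at the same rate as those still under observation. The result is then a proportion for a population in which nobody dies, not the proportion of patients who converted by a given month.

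Two things follow if deaths are censored. The reported proportion is too high in any arm with deaths before conversion. And if deaths differ between arms, in either direction, the part of the conversion difference that runs through mortality drops out of this comparison. The trial is meant to inform a later pragmatic trial, so the conversion proportions may be reused as planning figures. Hypotheses I and II also require that NAC does not interfere with the anti-TB regimen, and conversion is the main bacteriological evidence on that.

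**Working it through.** **Inputs from the article.** The Sample size section states that "the sample size for the proposed trial will be 20-per arm". Adding 10% gives 20 × 1.10 = 22 per arm and 3 × 22 = 66 in total, which reproduces the stated figure. There is no conversion rate, death rate or power figure to reproduce.

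**Assumed inputs.** Median time to conversion is 2 months. Six-month mortality d is 5%, 10% or 15%. Conversion and death are independent with constant hazards.

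**Formulas.** Conversion hazard c = ln 2 / 2 = 0.3466 per month. Death hazard m = −ln(1 − d) / 6.

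- One minus Kaplan-Meier with deaths censored: 1 − exp(−cT). At T = 6 this is 1 − 0.125 = 87.5%, whatever the mortality.
- Actual proportion converting (cumulative incidence): c/(c + m) × [1 − exp(−(c + m)T)].

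With d = 10%: m = 0.01756, c/(c + m) = 0.9518, and exp(−(c + m) × 6) = 0.125 × 0.90 = 0.1125. The cumulative incidence is 0.9518 × 0.8875 = 84.5%, so the overstatement is 3.0 points.

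| Six-month mortality (assumed) | Kaplan-Meier, deaths censored, 6 months | Cumulative incidence, 6 months | Overstatement, 6 months | Overstatement, 4 and 8 months |
|---|---|---|---|---|
| 5% | 87.5% | 86.0% | 1.5 | 1.0 and 1.9 |
| 10% | 87.5% | 84.5% | 3.0 | 2.0 and 3.7 |
| 15% | 87.5% | 82.9% | 4.6 | 3.1 and 5.7 |

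**Wider range.** Over median conversion times of 1 to 4 months and mortality of 2% to 20%, the overstatement at 6 months is 0.4 to 6.2 points.

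**Early deaths.** If all deaths fall in the first 2 months and the median conversion time stays at 2 months, the cumulative incidence at 6 months is 84.5%, 81.5% and 78.5% for mortality of 5%, 10% and 15%. The overstatement is then 3.0, 6.0 and 9.0 points.

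**Small-sample example.** Take 22 in an arm, two deaths before any conversion, and the other 20 all converting. With the deaths censored, Kaplan-Meier reaches 100%. The actual proportion is 20/22 = 91%.

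**Effect on a comparison.** With equal conversion hazards and mortality of 15% in control and 5% on NAC, the Kaplan-Meier difference is 0 and the cumulative-incidence difference is about 3 points (86.0% against 82.9%). With 10% against 5% it is 1.5 points.

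**Where the error comes from.** In a simulation of 200,000 patients (median 2 months, 10% mortality), Kaplan-Meier with deaths censored gave 87.6%. Kaplan-Meier with deaths kept at risk as non-converters gave 84.5%, equal to the crude proportion. The censoring rule causes the overstatement, not the estimator.

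**Set against precision.** At 85% converting with 22 per arm, the 95% half-width is 1.96 × √(0.85 × 0.15 / 22) = 14.9 points for one arm and 1.96 × √(2 × 0.85 × 0.15 / 22) = 21.1 points for a difference.

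**The case against.** The strongest reply is that the article never says deaths are censored. The rule may sit in a full protocol or analysis plan that is not shown, and keeping deaths at risk as non-converters removes the overstatement. That stands, and it is why the conclusion is conditional. It does not dispose of the point, because the article does commit to an estimator for a specific quantity, and that estimator's usual convention gives a different one.

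The separate rate at 4, 6 or 8 months also counts for the plan. With all randomised participants as the denominator and deaths counted as not converted, it has no such bias. But the article does not state that denominator, and multiple imputation, if applied to participants who died, would credit some of them with conversion.

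It is also fair to say that the hazard ratio and log-rank test are the more direct tools for asking whether NAC interferes with the regimen, since a cumulative incidence mixes that question with mortality. They should stay.

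A reader might infer that the analysis hides a mortality benefit of NAC, because the Discussion reports that "a large cohort study revealed that patients that received pulmonary TB treatment and NAC had a substantial reduction in 90-day all-cause mortality". The article does not support that. The citation is an association in one cohort, with no effect size and no statement that the patients had MDR-TB. A conversion curve is not the mortality analysis, and events are captured elsewhere: "Any AE (serious or non-serious) observed by the investigator or reported by the subject will be recorded".

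A reader might also put the overstatement at 4 to 12 points, from 80% conversion among survivors and 5% to 15% deaths (0.80 × 0.05 = 4 points; 0.80 × 0.15 = 12 points). That requires every death to come before conversion, which is an upper scenario.

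**Conclusion.** The point holds in a limited form and is minor. The article does not say how death before conversion enters its Kaplan-Meier estimate. If deaths are censored, the estimate exceeds the proportion it is said to measure and omits any between-arm difference that arises through mortality. The size rests on assumed inputs: about 1.5 to 4.6 points at 6 months for 5% to 15% mortality spread evenly and a 2-month median conversion time, and 3.0 to 9.0 points if the same deaths all fall in the first 2 months. In most of these scenarios that is well below the sampling error of a 22-patient arm, and the endpoint is secondary in a pilot. It still merits correction, because a confidence interval shows imprecision but not this bias. The article supports no claim that the analysis conceals an effect of NAC on mortality.

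**What to change.** - Estimate the proportion converting by each time point with the Aalen-Johansen cumulative incidence function, taking death before conversion as a competing event. With complete follow-up, keeping deaths at risk as non-converters to the end of the window is equivalent.
- For the 4, 6 and 8 month rates, state that all randomised participants form the denominator, that deaths before conversion count as not converted, and that these outcomes are not imputed.
- Keep the planned hazard ratio and log-rank test, described as cause-specific, for the question of interference with the anti-TB regimen.

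The cost is a sentence or two of analysis text. The data are already to be collected and the software is standard. Reported conversion will be slightly lower.
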